#### Sham acupuncture group

2.7.2

Participants in the control group will receive sham acupuncture treatment. Sham points, which are 1 cun lateral to Zhao Hai(KI 6), Da Zhong(KI 4), Tai Xi(KI 3), Tian Shu(ST 25), and Shang Ju Xu(ST 37), will be used to match real acupuncture points. The placebo needles chosen for this study are flat-tipped needles without a tip, which could not be pierced into the skin. In the meanwhile, an external patch device will fix the needles, which are visually pierced into the skin. When the blunt tip of the needle touches the skin, patients will feel a pricking sensation, but without the feeling of de qi. After the treatment, the acupuncturist will press the acupuncture point with a dry cotton ball so that the patient can feel the pulling out of the “needle.” It is worth pointing out that the sham acupuncture device used in this study has been granted a utility model patent by China National Intellectual Property Administration (the Patent Number: ZL 2023 20605629.3).

Participants in both groups will be provided with health education, attention to the dietary regimen, avoidance of irritating foods, and attention to emotional self-regulation. Participants will be asked to keep a stool diary in the study, which is recorded during the baseline period (weeks −1 and 0), the treatment period (weeks 3–8), and the follow-up period (weeks 11, 12, 19, and 20). Moreover, the researcher will instruct patients on how to complete the stool diary. All participants will receive 24 sessions of acupuncture or sham acupuncture three times a week for 8 weeks. All treatments will be performed after skin disinfection, and each treatment will last for 30 min. Meanwhile, every patient will be required to stay in the supine position and wear an eye mask during the treatment.

If the patient has had no bowel movement for 3 or more consecutive days, or if the patient has had serious physical discomfort due to the inability to defecate, he/she can take emergency treatment. To be specific, he/she is allowed to use 20 mL of Glycerine Enema (Glycerine Enema, H31021363, Shanghai Yunjia Huangpu Pharmaceutical Co., Ltd.; 20 mL/bottle). However, the patient is required to strictly record the dose and frequency of medication. At the same time, the investigators will record the patient’s medication in detail on the CRF.

### Primary outcomes

2.8

The primary outcome of the study is the treatment response rate, which is the proportion of participants with ≥3 mean weekly CSBMs over weeks 3–8. The CSBMs refers to the frequency of a bowel movement that occurs in the absence of laxatives or manipulation. In this study, the mean CSBMs at baseline is calculated by dividing the total number of CSBMs between weeks −1 and 0 by the number of weeks 2. Meanwhile, the mean CSBMs at week 8 is calculated by dividing the total number of CSBMs between weeks 3 and 8 by the number of weeks 6.

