### Inclusion criteria

2.3

For FC patients, the inclusion criteria are as follows:

(1) Meet Rome IV Diagnostic Criteria for Constipation and TCM Diagnostic Criteria of constipation with yin deficiency syndrome; (2) No gender restriction, age 60–80; (3) FC that is classified as mild or moderate (34); (4) Have not used any medicine for constipation at least 4 weeks before treatment (except emergency treatment); (5) Those who can understand various evaluation scales, complete the evaluation and cooperate with the completion of the planned course of treatment; (6) Sign the informed consent.

For healthy subjects, the inclusion criteria are as follows:

(1) No gender restriction, age 60–80; (2) No constipation-related symptoms after comprehensive assessment for enrolment; (3) No significant gastrointestinal symptoms (e.g., abdominal pain, diarrhea, blood in the stool, constipation, abdominal distension, etc.) are reported in the 4 weeks before enrolment; (4) No medication to promote or inhibit gastrointestinal motility within 4 weeks before enrolment; (5) No mental and intellectual abnormalities, able to understand the provisions of each scale and complete the assessment; (6) Agree to participate in the study and sign the written informed consent.

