### Secondary outcomes

2.9

The secondary outcomes include the following items: (1) The treatment response rate, which is the proportion of participants with ≥3 mean weekly CSBMs during another assessment period. It will be evaluated at weeks 4, 12 and 20. (2) The percentage of patients with ≥1 increase in mean weekly CSBMs from baseline. It will be evaluated at weeks 4, 8, 12 and 20. (3) The mean weekly CSBMs change from the baseline. It will be evaluated at weeks 4, 8, 12 and 20. (4) Patient Assessment of Constipation-Symptoms (PAC-SYM): a scale to assess the condition of the patient’s constipation-related symptoms. It will be evaluated at weeks 0 and 8. (5) Bristol Stool Scale: a scale to classify the patient’s voluntary bowel movement stool. It will be evaluated at week 0 and 8. (6) Patient Assessment of Constipation Quality of Life Questionnaire (PAC-QOL): a brief but comprehensive assessment of the daily life quality of patients with FC, containing 28 items. It will be evaluated at weeks 0 and 8. (7) Self-rating Anxiety Scale (SAS) (36): a measure of somatic symptoms associated with anxiety reactions. It will be evaluated at weeks 0 and 8. (8) Self-rating Depression Scale (SDS) (37): a self-rating scale to assess patients’ depression. It will be evaluated at weeks 0 and 8. (9) Weekly usage of emergency bowel medications: the proportions of participants using medications and doses for emergency treatment. It will be evaluated from week 1 to week 20.

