### Sample size calculation

2.12

The sample size is estimated based on the treatment response rate (the proportion of participants with ≥3 mean weekly CSBMs over weeks 3–8). According to the results of our pre-test, the treatment response rate in the treatment group at week 8 was 31.25% (5/16); The treatment response rate of the control group at week 8 was 6.25% (1/16). The test level was set at α = 0.05 (bilateral), and the test efficacy 1-β = 0.80. According to the calculation made by PASS 15.0, the sample size of each group was 39 cases. Considering the 20% shedding rate, 49 cases will be finally taken from each group, and a total of 98 cases will need to be enrolled in this study.

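### The primary response is an absolute level of 3 CSBMs per week and entry sets no baseline ceiling, so an unchanged participant already at that level counts as a responder in either arm

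*Protocol article*

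**What the plan says.** Section 2.8 of the protocol article defines the primary outcome as "the treatment response rate, which is the proportion of participants with ≥3 mean weekly CSBMs over weeks 3–8". The abstract and section 2.12 use the same threshold. Section 2.8 also explains how a baseline value is obtained: "the mean CSBMs at baseline is calculated by dividing the total number of CSBMs between weeks −1 and 0 by the number of weeks 2". That value does not enter the primary definition. Section 2.13 plans a chi-square or Fisher's exact test for the week 8 response rate, with no baseline term.

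Improvement is measured separately, as a secondary outcome in section 2.9: "The percentage of patients with ≥1 increase in mean weekly CSBMs from baseline". The mean change in weekly CSBMs is another secondary outcome. Both are assessed at week 8.

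For patients with constipation, section 2.3 requires "Meet Rome IV Diagnostic Criteria for Constipation and TCM Diagnostic Criteria of constipation with yin deficiency syndrome" and "FC that is classified as mild or moderate (34", together with age, medication, comprehension and consent conditions. Neither that list nor the exclusions in section 2.4 give a maximum number of CSBMs or bowel movements at baseline.

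**The concern.** Someone who averages 3 CSBMs per week in the baseline diary and 3 over weeks 3–8 has not changed, yet is counted as a treatment responder. So is someone who falls from 4 to 3. Nothing stated in the article prevents such a person from being enrolled.

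Three features make this more than a formal possibility:

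- Severe constipation is left out by the severity criterion, which can be expected to move enrolment nearer the threshold.
- The CSBM is described without mention of completeness: "The CSBMs refers to the frequency of a bowel movement that occurs in the absence of laxatives or manipulation". Read literally, 3 per week is then easier to reach at baseline.
- Table 1 puts eligibility screening at week −1, while the diary covers weeks −1 and 0. Screening as scheduled therefore comes before the diary is complete.

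Participants who respond whatever they receive add the same amount to both arms' rates. The difference shrinks, both proportions move towards values with larger variance, and the label no longer means that the patient responded.

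**Working it through.** **The plan's own figure.** Section 2.12 gives p1 = 5/16 = 0.3125, p2 = 1/16 = 0.0625, two-sided α = 0.05 and power 0.80. With p̄ = (0.3125 + 0.0625)/2 = 0.1875, the pooled formula without continuity correction is

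n = [1.960·√(2·0.1875·0.8125) + 0.842·√(0.3125·0.6875 + 0.0625·0.9375)]² / 0.25² = 37.1, rounded up to 38.

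The stated 39 is within one patient of this. Dropout: 39/0.80 = 48.75, so 49 per arm and 98 in total, as stated. No figure in section 2.12 is disputed.

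**Dilution.** Let q be the share of each arm that enters at 3 or more CSBMs per week and stays there. The documents give no value for q, so every value below is an assumption.

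**Reading A: the pre-test rates describe only participants below the threshold at entry.** Each trial rate becomes q + (1 − q)p, and the difference becomes (1 − q)·0.25. Power is by exact binomial enumeration of the uncorrected chi-square test.

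| q | Acupuncture | Sham | Difference | Power, 39 per arm | Power, 49 per arm |
|---|---|---|---|---|---|
| 0 | 31.3% | 6.3% | 25.0 points | 85% | 93% |
| 5% | 34.7% | 10.9% | 23.8 points | 73% | 82% |
| 10% | 38.1% | 15.6% | 22.5 points | 63% | 72% |
| 20% | 45.0% | 25.0% | 20.0 points | 46% | 54% |

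The normal approximation gives similar values at 39 per arm: 82%, 71%, 61% and 46%.

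**Reading B: the pre-test used the trial's entry rules, so its rates already contain these participants.** The planned power then already reflects the dilution, and no further loss occurs. Turning the formula round shows what removing them would gain. For q = 4%:

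- acupuncture (0.3125 − 0.04)/0.96 = 28.4%
- sham (0.0625 − 0.04)/0.96 = 2.3%

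Power at 39 per arm rises from 85% to about 95%.

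**What the pre-test says about q.** Under Reading B a true sham rate of 6.25% caps q at 6.25%, because these participants are all responders. Under Reading A, q = 20% implies a sham rate of 25%, and the probability of at most 1 responder in 16 is then 0.75¹⁶ + 16·0.25·0.75¹⁵ = 6.3%. The exact 95% interval for 1/16 is 0.2% to 30%. The pre-test therefore neither supports a large share nor excludes one.

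**The case against.** The strongest objection is that the power loss may be counted twice. Section 2.12 reports the pre-test rates under the very endpoint the trial will use, so anyone in the pre-test who was already at threshold and stayed there is inside 5/16 and 1/16. If the entry rules were the same, which is not stated, the loss in Reading A does not arise. This stands, and the table must be read as conditional.

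It can also be said that Rome IV or the cited severity grading may already limit stool frequency. The article does not give the content of either, so this cannot be judged from it. That the diary plays no part in screening is likewise an inference from silence in a condensed article. Both points limit how firmly one can say that such patients will be enrolled. Neither supplies a stated ceiling.

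Finally, the threshold is used consistently, and the week 8 secondary outcomes let a reader see whether participants improved. That is fair: the plan does not contradict itself, and the information is collected. It does not repair the meaning of the primary result.

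A reader might infer that the comparison is biased, or that a chance imbalance of two or three such participants would invalidate it. The documents do not support either. Randomization balances these participants in expectation, chance imbalance is already covered by the test's error rate, and dilution works against finding a benefit of acupuncture.

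**Conclusion.** The point holds as a weakness of definition. Under sections 2.3, 2.4 and 2.8 together, a participant already at 3 or more CSBMs per week who does not improve is a responder in either arm. The consequence is a diluted difference and an unclear meaning of response, without bias towards one arm.

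The size cannot be fixed from the documents. On the assumption that the pre-test rates exclude such participants, a 5% share costs about 12 points of power at 39 per arm and about 10 at 49 per arm (from the unrounded 92.5% to 82.5%). If the pre-test rates include them, there is no loss beyond what is already planned.

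It would be tempting to conclude that the trial is underpowered. That does not follow: even under the unfavourable reading, a 5% share leaves 82% power at the 49 per arm that will be enrolled, above the planned 80%. The case for change rests on a clearer endpoint at low cost.

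**What to change.** Add to section 2.3 a requirement that mean weekly CSBMs be below 3 on the completed two-week baseline diary (weeks −1 and 0), and state that this is checked before the allocation envelope is opened. If the existing criteria already imply such a limit, say so explicitly. The diary is already collected, so the cost is one line and a few screened patients turned away. Power is higher with this limit than without it under either reading.

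If entry cannot change, keep the current primary endpoint and pre-specify a sensitivity analysis that counts as responders those with at least 3 CSBMs per week over weeks 3–8 and an increase of at least 1 from baseline. This needs no new data.

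Making that composite the primary endpoint is the weaker option. The 5/16 and 1/16 rates were measured under the current definition, so the sample size would have to be rechecked against rates for the new one.

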### Statistical methods

2.13

Statistical analysis will use SPSS 26.0 according to an intention-to-treat analysis. The missing data of the primary outcome will be filled in with the last observation data, while the missing data of safety evaluation will not be filled in. Continuous variables will be expressed as mean ± standard deviation (SD) or median and interquartile range (IQR). The categorical variables will be presented as frequencies or percentages. The *p* value is obtained according to the statistics, and the difference is statistically significant when *p* < 0.05.

Categorical variables, including the treatment response rate (week 8) and the incidence of AEs, will be analyzed using Chi-Square or Fisher’s exact tests. Generalized Estimating Equations (GEE) will be used to compare the data measured repeatedly, including the treatment response rate (week 4, 12, 20), the percentage of patients with ≥1 increase in mean weekly CSBMs from baseline, the mean weekly CSBMs change and Weekly usage of emergency bowel medications. Unpaired *t*-test or Mann–Whitney U test will be used to compare continuous variables between groups, including the mean changes of PAC-SYM, Bristol Stool Scale, PAC-QOL, SAS, and SDS scale.

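### The week 8 point in the CSBM repeated-measures analyses is a weeks 3–8 mean, so it overlaps week 4 and spans three times the diary window of weeks 12 and 20

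*Protocol article*

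**What the plan says.** All references are to the protocol article.

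- **Primary outcomes (2.8).** The primary endpoint is "the proportion of participants with ≥3 mean weekly CSBMs over weeks 3–8". The same paragraph gives two formulas. Baseline is obtained by "dividing the total number of CSBMs between weeks −1 and 0 by the number of weeks 2". For the end of treatment, the "mean CSBMs at week 8 is calculated by dividing the total number of CSBMs between weeks 3 and 8" by 6. No other week 8 CSBM value is defined.
- **Sham acupuncture group (2.7.2).** After the two baseline weeks, the stool diary is kept in "the treatment period (weeks 3–8), and the follow-up period (weeks 11, 12, 19, and 20". Weeks 1 and 2 are not recorded.
- **Secondary outcomes (2.9).** For the change outcome: "The mean weekly CSBMs change from the baseline. It will be evaluated at weeks 4, 8, 12 and 20". The outcome of at least one extra CSBM per week has the same four time points. The secondary response rate (at least 3 per week) does not: "It will be evaluated at weeks 4, 12 and 20". Table 1 agrees.
- **Statistical methods (2.13).** "Generalized Estimating Equations (GEE) will be used to compare the data measured repeatedly". The list covers the response rate at weeks 4, 12 and 20, the extra-CSBM outcome and mean change. The week 8 response rate is tested separately by chi-square or Fisher's exact test.

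**The concern.** A repeated-measures model estimates how an outcome, and the difference between arms, moves from one visit to the next. That reading assumes that the same quantity is measured at each visit. Under the stated formula, one of the four points is an average over most of the treatment period, while the other three can only be short windows. Part of the long average is also the diary data available for the first point.

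Two things are at stake. First, if the effect builds during treatment, the week 8 mean lags behind the level reached by the end of treatment. A true decline afterwards could then look like stability or a gain. Second, for an outcome defined by a cut-off, the length of the averaging window changes the proportion that crosses it, even when nothing about the patients has changed. With 12 weeks of follow-up planned, statements about time course and durability are likely.

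**Working it through.** **Plan's own figure.** The article gives no figure for this point. Its only calculation, the sample size in 2.12, reproduces closely. With 5/16 against 1/16, two-sided 0.05 and 80% power, the pooled normal formula gives 38 per group (39 stated), and 39/0.8 = 48.75, rounded up to 49. It rests on the weeks 3–8 endpoint, which is not in question.

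**Step 1: windows.** The week 8 and baseline windows are stated in 2.8. The others are the most that the diary in 2.7.2 allows; the article does not write them out.

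| Point | Diary weeks | Length |
|---|---|---|
| Baseline | −1, 0 | 2 |
| Week 4 | 3–4 (at most) | 2 |
| Week 8 | 3–8 | 6 |
| Week 12 | 11–12 | 2 |
| Week 20 | 19–20 | 2 |

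Overlap of week 8 with week 4: 2/6 = one third. Length ratio of week 8 to week 12 or week 20: 6/2 = 3.

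**Step 2: mean change.** Let the effect average d1 in weeks 3–4 and d2 in weeks 5–8. Week 8 then shows (2·d1 + 4·d2)/6 = (d1 + 2·d2)/3. The rise from week 4 is (d1 + 2·d2)/3 − d1 = (2/3)(d2 − d1), so one third of it is lost. If d1 = d2, nothing is lost.

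An assumed example: weekly means of 1.0, 1.3, 1.6, 1.9, 2.2 and 2.5 over weeks 3–8, then 2.2 in weeks 11–12 and 1.9 in weeks 19–20.
- Weeks 3–4: 1.15. Weeks 5–8: 2.05. Week 8 as defined: (1.15 + 2 × 2.05)/3 = 1.75.
- Weeks 7–8: (2.2 + 2.5)/2 = 2.35.
- As defined, the series is 1.15, 1.75, 2.20, 1.90, so both follow-up points lie above week 8. On equal windows it is 1.15, 2.35, 2.20, 1.90, a decline after treatment.

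**Step 3: at least one extra CSBM per week.** Assume Poisson counts, a true baseline of 1/week and a true gain δ. The baseline count B is Poisson with mean 2. The later count X over w weeks is Poisson with mean w(1 + δ). A patient counts as improved if X/w − B/2 ≥ 1, so the proportion is the sum over b of P(B = b) · P(X ≥ w(1 + b/2)). The cut-off for X is 2 + b on two weeks and 6 + 3b on six.

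| True gain δ | 2-week window | 6-week window |
|---|---|---|
| 0 | 22% | 12% |
| 0.5 | 40% | 33% |
| 1 | 57% | 55% |
| 1.5 | 71% | 74% |
| 2 | 81% | 86% |

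The artefact changes sign as the gain grows, so it need not cancel between arms. For example, with no change in one arm and a constant gain of 2 in the other, the difference between arms is 81 − 22 = 59 points on two weeks and 86 − 12 = 74 points on six, although the true effect is the same.

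**Step 4: response at 3 or more per week.** This GEE uses only weeks 4, 12 and 20, all of two weeks at most. Window length matters only when the weeks 3–8 primary result is set beside weeks 12 and 20. With Poisson counts, P(X ≥ 6) on two weeks against P(X ≥ 18) on six is 21.5% against 6.3% at 2/week, but 70% against 77% at 3.5/week. With between-patient variation added (assumed coefficient of variation 0.5), the gap at a mean of 2/week shrinks to 25.4% against 19.1%.

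**The case against.** The strongest case on the other side has five parts.

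- **No stated inference is harmed.** The article names no week 4 against week 8 contrast and no durability test, and both arms use the same window, so group comparisons at any single point are valid. The second half stands in full. The first stands in part: the GEE is announced as a comparison of repeated data, and its time and group-by-time terms are where the mismatch enters.
- **Mean change is not biased by window length alone.** This stands. Only the variance differs unless the rate moves within weeks 3–8, and nothing in the article says that it does.
- **Overlap is only within-patient correlation, which GEE handles.** This is right for the standard errors. It does not alter what the week 8 mean represents.
- **The 2-week windows are inferred.** This also stands, and a fuller document might set them out. But the diary permits nothing longer at weeks 4, 12 and 20, and the week 8 formula is stated outright.
- **The response-rate GEE leaves out week 8.** This is correct, and it limits the point to the other two CSBM outcomes.

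A reader might infer three stronger claims that the document does not support. One is that follow-up response will be inflated in general; the direction reverses above the cut-off. Another is that there is no end-of-treatment measure; PAC-SYM, the Bristol scale, PAC-QOL, SAS and SDS are all taken at week 8, and only a separate CSBM value is missing. The third is that the primary result is compromised; a weeks 3–8 response rate is a legitimate endpoint.

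**Conclusion.** The point holds for two secondary analyses: the GEE of at least one extra CSBM, and the GEE of mean CSBM change. There, week 8 is not comparable with weeks 4, 12 and 20, so time and group-by-time effects mix real change with a change of window.

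For mean change, the week 4 to week 8 rise is shown at two thirds of the difference between weeks 3–4 and weeks 5–8, if the effect changes in that period; otherwise there is no bias. For the extra-CSBM outcome, the shift from window length alone runs from 10 points up (22% against 12%) to 5 points down (81% against 86%) over the gains tried. These sizes are illustrative: they rest on Poisson counts and an assumed baseline of 1/week, neither of which comes from the article.

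For response at 3 or more per week, only an informal comparison of the primary result with weeks 12 and 20 is affected. The primary endpoint, its test and the sample size stand as planned.

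**What to change.** Keep weeks 3–8 for the primary outcome. In 2.9 or 2.13, state that the GEE of the extra-CSBM and mean-change outcomes uses weeks 3–4, 7–8, 11–12 and 19–20 for the week 4, 8, 12 and 20 points. For any statement on durability of response, compare weeks 12 and 20 with a separately labelled weeks 7–8 response rate, not with the weeks 3–8 primary result.

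The cost is a sentence or two. All these diary weeks are already collected, and the sample size does not change. There are two downsides. The week 8 secondary values become somewhat noisier: in a simulation with a mean of 2/week and the same assumed between-patient variation, the standard deviation is 1.41 on two weeks against 1.15 on six. There will also be a second week 8 response figure, which must be labelled so that it is not mistaken for the primary.
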